## **9. ASSESSMENT OF MORBIDITY:**

#### **9.1. Parameters to be measured:**

Hb level and weight at baseline, 6M and 12M.

9.2. Methods: Hb level and weight will be measured as described on sections 6.2.4. and 6.2.5.

9.3. Analysis:

- Variation of Hb level (as described above) will be compared between the 2 treatment regimens, PZQ 40mg/Kg and 60mg/Kg.
- Variation of weight will be compared between the 2 treatment regimens, PZQ 40mg/Kg and 60mg/Kg.

## **10. DATA PROCESSING AND ANALYSIS**

The data will be double entered into a computer using dBase programme by two different data entry clerks and the entered data will then be verified and cleaned before being subjected to analysis using STATA.

10.1. Analysis of data: Chi- square or Fisher's exact test will be used for comparison of proportions (ex. cure rate & egg reduction rate, frequency of AEs and severity of AEs) and Student's t test for comparison of means (geometric mean egg output, variation of Hb level and weight) in the two treatment groups (PZQ 40mg/kg and 60mg/kg).

10.2. Sample size:

Assuming the cure rate of a standard dosage (40mg) of Praziquantel is 60% and increasing the dosage to 60mg would improve cure rate to *at least* 80%, a sample size of 91 infected schoolchildren per study group will be needed. This sample size will give a study power of 80% at 5% significance level. Considering a drop out of about 30% due to loss to follow-up or medical grounds, 118 study subjects will be needed for each study group making a total of 236 schoolchildren.

10.3. Quality Control:

During laboratory examination of stool and urine specimens, a 10% sample of specimens will be re-examined by an independent technician (one who is not part of the research team) every day and results compared to see the degree of agreement.

10.3.1. For Kato-Katz examinations:

10% of the slides read by each microscopist will be randomly selected and re-examined by an experienced microscopist designated by the PI.

*For cure rate* (agreement between positive/negative slides) the maximum discordance rate acceptable will be 5%. Above 5% all slides will have to be read by the experienced microscopist.

*For infection intensity*, levels of infection will be defined as:

| Number of eggs/slide | Approximate egg count/g of stools |
|----------------------|-----------------------------------|
| 1-4                  | ~ 1-100                           |
| 5-12                 | ~ 100-300                         |
| 13-25                | ~ 300-600                         |
| 26-41                | ~ 600-1.000                       |
| >41                  | ~ 1.000                           |

Disagreement will be defined when the 2 readings result in different levels of infection, according to this classification. The maximum level of disagreement accepted will be 5%.

If the conditions for agreement are not met, all slides will be read a second time and the results of the second reading will be considered for the study.

If the conditions for agreement are met, the results of the first reading will be used.

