## **2. OBJECTIVES**

The main objective of this study is to determine if higher dose of praziquantel at 60 mg/kg will improve treatment efficacy with an adequate safety profile, in comparison with standard regimen of praziquantel at 40mg/kg.

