  - a) Egg reduction rate at 21 days after treatment for the PZQ 60mg/Kg and PZQ 40mg/Kg groups.
  - b) Comparison of frequency and severity of adverse events during the 4 hours after treatment, 24 hours and 21 days, for the PZQ 60mg/Kg and PZQ 40mg/Kg groups.
  - c) Comparison of the variation of hemoglobin (Hb) level at 21 days, 6 months and 12 months after treatment (as related to the baseline measurement), for the PZQ 60mg/Kg and PZQ 40mg/Kg groups.
  - d) Comparison of the variation of weight at 6 months and 12 months after treatment (as related to the baseline measurement), for the PZQ 60mg/Kg and PZQ 40mg/Kg groups.

The flow-chart below illustrates the study design:

[figure not shown]

Rapport with government and community leaders at district, ward, village and school levels will be established in the study area. Informed Consent will be obtained for each participant. For children considered minors written Informed Consent will be obtained from their guardians. Schoolchildren meeting the screening criteria will be recruited continuously, subjects will be examined quantitatively for *S mansoni* ova and semi-quantitatively for *S haematobium*. Two stool samples (2 Kato Katz slides will be prepared from each sample) and one urine sample will be collected within 5 days. Those who fulfill the inclusion and exclusion criteria for enrolment in the trial will be randomized to receive treatment with PZQ within 7 days (+/-1 day).

See Appendix 1 for the schedule of activities. It is estimated that 800 school children will be examined during the baseline study within one month. It is expected that about 240 children (30%) will fulfill the criteria for enrollment in the trial. Participants with positive *Schistosoma spp.* diagnosis who do not fulfill the inclusion and exclusion criteria will be treated with the standard treatment of a single dose of PZQ 40mg/Kg.

Schoolchildren in the treatment groups will be followed up for a total of 12 months post-treatment.

The following baseline screening and follow up visits will be done. As shown in Appendix 1 the baseline study is scheduled to last 23 days. Since enrollment is done continuously, activities of D0 will start on the 8th day after screening and activities of D1 on the 9th day and run concurrently with the screening.

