## **8. ASSESSMENT OF SAFETY:**

### **Adverse Events**

#### **8.1. Parameters to be measured:**

Occurrence and severity of Adverse Event at 4 hours, 24hs, and 21 days after treatment.

**8.2. Methods:** All AEs will be characterized for: severity grading, relationship to the treatment and seriousness.

Treatment with PZQ will be done in the morning of D0 and the research team will remain at the treatment centre until 18.00 hr. Children administered with PZQ will be observed for at least 4 hours before leaving the school compound.

All schoolchildren enrolled in the study will be administered with a questionnaire 4 hours after treatment for the following signs and symptoms: abdominal pain, nausea, vomiting, diarrhoea, anorexia, fever, headache, dizziness and allergic reaction. Each symptom will be graded as described in Table 1 of Appendix 3. Other symptoms not listed in Table 1 will be graded for severity according to classification in Table 2 of Appendix 3. Also, causal assessment for the adverse events in relation to the drug will be done as: not related, unlikely, possible, probable, most probable or insufficient data to assess (see definitions in Appendix 4). On the following day (Day 1), that is, 24 hours post-treatment, all schoolchildren who received PZQ on Day 0 will be interviewed using the same questionnaire to determine whether they experienced any adverse events. The questionnaire will be repeated on day 21-post treatment. In addition, on day 21 Hb will be measured by digital hemoglobinometer (hemocue) to determine whether increased dosage of PZQ has adverse effects on haemoglobin level.

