All AEs will be evaluated for seriousness according to the definitions described in Appendix 5. Any immediate serious adverse events will be managed using a resuscitation kit comprising of intravenous N/saline, Adrenaline, Hydrocortisone and carefully monitored until the adverse event disappears completely. All AEs will be monitored and followed-up until resolution. An adverse event likely to be related to the administration of the investigation product which persists to the end of the trial or any serious adverse event occurring after the termination of the trial and likely to be related to the product, will be followed up by the study physicians until its complete disappearance. The causality of such a serious adverse event will be investigated and recorded. Within 24 hours of its occurrence the Principal Investigator will report such serious adverse event to the TDR Clinical Monitor and TDR Clinical Coordinator by a SAE alert form. A complete SAE report will be sent within 5 working days to the Clinical Monitor and Clinical Coordinator. During the forwarding of the information the anonymity of the subject will be maintained. All this will be done in compliance to applicable regulatory requirements related to the reporting of unexpected serious adverse drug reactions to the regulatory authority(ties) and the ICB/IRB.

**8.3. Analysis:** The frequency and severity of AEs will be compared between the 2 treatment regimens, PZQ 40mg/Kg and 60mg/Kg.

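### Adverse events are compared only by a difference test, in a trial sized for cure rate; a non-significant result could not by itself support an adequate safety profile at 60 mg/kg

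*Protocol*

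**What the plan says.** Section 2 of the protocol sets the main objective as finding out whether a "higher dose of praziquantel at 60 mg/kg will improve treatment efficacy with an adequate safety profile, in comparison with standard regimen" at 40 mg/kg. Section 3.2 repeats this in the design statement and lists as secondary endpoint (b): "Comparison of frequency and severity of adverse events during the 4 hours after treatment, 24 hours and 21 days".

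Two places describe the AE analysis. Section 8.3 says: "The frequency and severity of AEs will be compared between the 2 treatment regimens, PZQ 40mg/Kg and 60mg/Kg". Section 10.1 names the method: "Chi- square or Fisher's exact test will be used for comparison of proportions (ex. cure rate & egg reduction rate, frequency of AEs and severity of" such events.

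Section 10.2 derives 91 per group from cure rates of 60% and 80%, says of it "This sample size will give a study power of 80% at 5% significance level", and raises the number to 118 per group for losses.

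The protocol assumes no AE rate, and it does not say what excess of AEs would still count as adequate.

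Safety has a second quantitative measure. Under section 8.2, haemoglobin is measured on day 21 "to determine whether increased dosage of PZQ has adverse effects on haemoglobin level", and section 10.1 assigns Student's t test to haemoglobin change.

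**The concern.** An adequate safety profile relative to the standard dose means that any excess of harm is small enough to accept. A difference test answers another question, namely whether the data are incompatible with no difference at all. A small p-value would signal harm. A large one shows only that harm was not detected, and how much that is worth depends on the excess the trial could have detected. The number of children was chosen for a 20-point gain in cure, so nothing in the design ensures that smaller but relevant AE excesses would show.

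The trial would inform use of a 50% higher dose (60 v 40 mg/kg) in schoolchildren, the group in which section 3.2 expects it to be used. If the AE comparison came out non-significant, the stated analysis would give the report no figure for how large an excess remains possible. The safety half of the objective would then go unanswered.

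**Working it through.** **1. The protocol's own figure.** Inputs from section 10.2: 60% v 80%, 80% power, 5% level (two-sided assumed; it reproduces the result).

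n = [1.96·√(2·0.7·0.3) + 0.842·√(0.6·0.4 + 0.8·0.2)]² / 0.2² = 81.2, so 82 per arm. With continuity correction, (81.2/4)·[1 + √(1 + 4/(81.2·0.2))]² = 90.9, so 91. Then 91 × 1.3 = 118.3, hence 118. The stated numbers reproduce, and cure rate is the only outcome that enters them.

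**2. Chance that the AE test misses a real excess.** Inputs: 118 per arm (section 10.2), chi-square or Fisher (section 10.1), two-sided 5%. The AE rates are assumptions.

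Normal approximation: miss = 1 − Φ{[d·√n − 1.96·√(2·p̄(1−p̄))] / √(p₁(1−p₁) + p₂(1−p₂))}. For 20% v 30%: [0.1 × 10.863 − 1.96 × √0.375] / √0.37 = (1.086 − 1.200) / 0.608 = −0.187, so the miss rate is 57%.

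Exact enumeration of both binomial distributions gives:

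| AE rate, 40 v 60 mg/kg | Missed by uncorrected chi-square | Missed by Fisher |
|---|---|---|
| 10% v 20% | 42% | 49% |
| 20% v 30% | 57% | 63% |
| 30% v 40% | 64% | 69% |
| 40% v 50% | 66% | 70% |
| 50% v 60% | 66% | 70% |

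**3. Sensitivity to the assumptions.** Same method, 118 per arm, chi-square / Fisher: 5% v 10%, 68% / 78%; 5% v 15%, 24% / 34%; 30% v 50%, 11% / 14%; 1% v 3%, 83% / 95%. With 91 per arm, 10% v 20% is missed 53% / 60% of the time. The result therefore ranges from about one in ten to almost always, depending on rates that the protocol does not give.

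**4. What a non-significant result can hide.** Take invented counts of 35/118 at 40 mg/kg and 49/118 at 60 mg/kg (30% v 42%). Chi-square gives p = 0.057 and Fisher p = 0.077. The excess is 14/118 = 11.9 points, with a Newcombe 95% interval from −0.3 to 23.6 points. For rare events, if no child among 118 has a severe event, the one-sided 95% upper limit is still 1 − 0.05^(1/118) = 2.5%.

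**5. What an interval can deliver at this size.** With equal true rates p, the 95% half-width is 1.96·√(2p(1−p)/118): 7.7, 10.2, 11.7 and 12.8 points at p = 10%, 20%, 30% and 50%. Excluding a given excess with 80% power at one-sided 2.5% needs n = (1.96 + 0.842)²·2p(1−p)/m² per arm. For an illustrative m of 10 points that is 142, 252, 330 and 393 at those rates; for 15 points it is 63, 112, 147 and 175. So 118 per arm can exclude only fairly large excesses, and the report should make that visible.

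**6. Haemoglobin.** A t test misses a half-standard-deviation difference about 3% of the time at 118 per arm and 11% at 82 per arm. This measure is outside the point.

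**The case against.** The strongest reply is that the protocol states no bad decision rule. It says AEs will be compared and names conventional tests, which do not prevent anyone from reporting differences and intervals, and a statistical analysis plan that is not at hand may require them. This stands in part. A reader might infer that p > 0.05 will be declared safe, but no section says so. What remains is that the protocol does fix an AE method, and that method does not answer its own objective.

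Second, safety does not rest on chi-square or Fisher tests alone. Day-21 haemoglobin has its own test, and events are graded for severity, causality and seriousness, with serious events reported and followed up. That is correct, so the stronger reading that all of safety hangs on those tests fails. But grading and reporting characterise individual events and set no criterion between arms.

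Third, no single miss rate belongs to this trial, because the AE rates are assumed. That also stands, and the figures should be quoted only with their scenarios.

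Fourth, AEs are a secondary endpoint, and sizing on the primary one is normal. Agreed: the sample size is not at fault, and a note that the 80% power refers to cure would be editorial.

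Fifth, nine solicited symptoms at three time points give many chances of a signal, so a general rise in harm is less likely to leave every test non-significant. True, but more tests also raise the chance of false signals, and a set of p-values still puts no upper bound on the excess.

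**Conclusion.** The point holds in a limited form. The only between-arm AE analysis in the protocol is a difference test, with no estimate, confidence limit or acceptable excess, while the main objective asks for adequate safety relative to 40 mg/kg. A non-significant AE test could not by itself support that conclusion. For a 10-point excess from control rates of 10% to 50%, the miss rate is about 42% to 66% with chi-square and 49% to 70% with Fisher, assuming 118 per arm, a two-sided 5% level and one test at a time; other assumptions widen the range. The documents do not show that the sponsor intends to read non-significance as safety. The change is worth making because it answers the stated objective at almost no cost.

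**What to change.** In sections 8.3 and 10.1, report the risk difference (60 minus 40 mg/kg) with its two-sided 95% confidence interval, for example Newcombe's, for two measures: the proportion of children with any AE by 24 hours, and the proportion with any grade 3–4 AE. Give an exact upper limit where no event is seen. State that the conclusion on an adequate safety profile will rest on the upper confidence limit, read against an acceptable excess that the sponsor sets before unblinding, and not on the p-value. The chi-square or Fisher result may still be shown beside the interval.

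The cost is a few sentences and a few intervals from data already planned. The sponsor must also commit to an acceptable excess, which is a clinical judgement this review does not make. The small downside is a more guarded safety conclusion, because the limits will be wide.

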#### 7.2. Methods for assessing efficacy:

- Cure rate will be estimated as the proportion of subjects with negative result at 21 days after treatment.
- Egg reduction rate at 21 days after treatment will be estimated through the following formula:  
 $[1 - (\text{epg2} / \text{epg1}) \times 100]$  where epg1 and epg2 are the geometric mean of  $\log_{10}$  transformed (x+1) numbers of eggs per gram of faeces at the screening survey and the 21st day post-treatment survey.

The same calculations of cure rate and egg reduction rate will be estimated for the 6M and 12M follow-up in order to estimate reinfection rates.

7.3. Analysis: The cure rate and egg reduction rate will be compared between the 2 treatment regimens, PZQ 40mg/Kg and 60mg/Kg.

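### The egg reduction rate is assigned a test for proportions although it is a ratio of group means, and its formula is misprinted and leaves the scale of the mean open

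*Protocol*

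**What the plan says.** Section 3.2 of the protocol lists as its first secondary endpoint: "Egg reduction rate at 21 days after treatment for the PZQ 60mg/Kg and PZQ 40mg/Kg groups". Objective 2.2 and section 7.3 confirm that the two regimens are to be compared on it.

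Section 7.1 takes each child's egg count as the mean of four Kato-Katz slides. Section 7.2 then gives the ERR formula as [1 - (epg2/epg1) x 100], with the factor 100 inside the bracket and attached to the ratio. It adds that "epg1 and epg2 are the geometric mean of" log10-transformed (x+1) counts, at screening and at day 21. No return to the egg scale is mentioned. The same calculation is to be reused at 6 and 12 months.

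Section 10.1 assigns the tests in one sentence. Chi-square or Fisher's exact test "will be used for comparison of proportions (ex. cure rate & egg reduction rate, frequency of AEs and severity of AEs"). The rest of the sentence assigns "Student's t test for comparison of means (geometric mean egg output, variation of Hb level and weight").

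**The concern.** Chi-square and Fisher's exact test compare counts of units that did or did not have an event. Cure rate fits this: so many children negative out of so many examined. ERR does not. It is one number per arm, a ratio of two means, and its sampling error comes from the spread of egg counts between children. That it is printed as a percentage does not make it a binomial proportion.

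So the protocol names, for its first-listed secondary efficacy endpoint, a test that cannot be carried out without inventing a denominator. The estimate has a problem as well: the printed bracket does not give a percentage reduction, and the missing back-transformation leaves two plausible computations that give quite different figures. If these choices are made after the data are seen, the reported ERR and its p-value depend on whoever runs the analysis, and the ambiguity carries through to 6 and 12 months.

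**Working it through.** **The plan's own figure.** The protocol gives no power or sample-size figure for ERR. Its only figure is 91 per group for cure rates of 60% v 80%, 80% power and 5% significance (section 10.2). For a two-sided test, n = [1.96 x sqrt(2 x 0.7 x 0.3) + 0.842 x sqrt(0.24 + 0.16)]^2 / 0.2^2 = 81.2, rounded up to 82. The continuity correction gives (81.2/4) x [1 + sqrt(1 + 4/(81.2 x 0.2))]^2 = 91. The figure is reproduced, and nothing below alters it.

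**1. The named test has no fixed unit.** Take ERR 95% v 99% as an illustration.
- Children as the unit, 91 per arm: 0.95 x 91 rounds to 86 and 0.99 x 91 to 90. Fisher on 86/91 v 90/91 gives p = 0.21.
- Eggs as the unit, assuming 300 per child: 91 x 300 = 27,300 per arm, so 25,935 v 27,027. Chi-square gives p of about 3e-165.

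For ERR 90% v 97% the two answers are p = 0.13 (82/91 v 88/91) and about 3e-241. The ERR values within each pair are identical; only the invented denominator differs. The protocol does not choose between them, and neither reflects the variation in egg counts between children.

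**2. The bracket.** With illustrative means:

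| epg1 | epg2 | As printed, 1 - (epg2/epg1) x 100 | Intended, (1 - epg2/epg1) x 100 |
|---|---|---|---|
| 300 | 3 | 0 | 99 |
| 300 | 15 | -4 | 95 |
| 300 | 60 | -19 | 80 |

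**3. The missing back-transformation.** Assumed inputs: baseline geometric mean (GM) 390 epg in both arms and GM 60 epg among children not cured. The cure rates of 60% v 80% are those of section 10.2. A cured child contributes log10(0 + 1) = 0.
- Baseline mean log: log10(391) = 2.592.
- Mean log among the uncured: log10(61) = 1.785.
- Day-21 mean log: 0.4 x 1.785 = 0.714 at 40 mg/kg; 0.2 x 1.785 = 0.357 at 60 mg/kg.
- Back-transformed day-21 GM: 10^0.714 - 1 = 4.18; 10^0.357 - 1 = 1.28.

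| Reading of epg | 40 mg/kg | 60 mg/kg |
|---|---|---|
| Back-transformed, 100 x (1 - GM2/GM1) | 1 - 4.18/390: 98.9% | 1 - 1.28/390: 99.7% |
| Ratio of mean logs | 1 - 0.714/2.592: 72.5% | 1 - 0.357/2.592: 86.2% |

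The gap between arms is 0.8 percentage points on one reading and 13.7 on the other, from the same data.

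**4. The t test in the same sentence.** This was simulated with 91 per arm and an assumed lognormal baseline centred near 250 epg. A t test on day-21 log10(epg+1) had type I error of about 5%. It rejected in 77% of trials at cure 60% v 80%, and in 72% at cure 30% v 50% with higher residual counts. That planned comparison works, provided it is run on log counts.

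**The case against.** The strongest reply is that a valid egg-count comparison is already in the plan. The sentence that misassigns ERR also gives geometric mean egg output to a t test, and that is the quantity from which ERR is built. This stands, and it limits the harm. It does not remove the error: ERR is still listed under a test that does not apply to it, and nothing says which of the two tests answers objective 2.2.

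A second reply is that the bracket is an obvious slip, since nobody would report an ERR of -4. This also stands. A reader might conclude that the formula is unusable or the result meaningless. The documents do not support that, because the intended form is evident from the endpoint's name and the estimate is recoverable once back-transformation is stated. Similarly, a literal geometric mean of the logs would be zero as soon as one child is cured, giving 100% in both arms. That reading is strained, because 1 is added precisely so that zero counts can enter a log-based mean.

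A reader might also infer that the chi-square test could never detect an ERR difference. With children as the unit, simulated rejection was indeed 0% to 8%, but that follows from assumed inputs and an arbitrary denominator. The accurate statement is that the test is undefined.

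Finally, it might be said that the Hb and weight t tests ignore baseline. They do not: section 3.2 defines both variations relative to the baseline measurement.

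**Conclusion.** The point holds as wrong wording in two places. Section 10.1 names an invalid test for secondary endpoint a), and section 7.2 misprints the ERR formula and leaves the scale of the mean unstated. The p-value for ERR 95% v 99% can be 0.21 or below 1e-160 according to the unit adopted. The estimates can be 98.9% v 99.7% or 72.5% v 86.2% according to the reading of epg. The 300 eggs per child, the baseline GM of 390 and the residual GM of 60 are assumptions; the cure rates and the 91 per group are the protocol's. Other inputs would change these sizes, but not the lack of a denominator or the ambiguity.

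The primary cure-rate comparison by chi-square or Fisher, and its sample size, are untouched. It would also go too far to call ERR the main support for the cure-rate result: the protocol only lists it first among the secondary endpoints. This should be fixed before analysis, but it does not threaten the trial's main conclusion.

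**What to change.** - In section 7.2, define ERR = 100 x (1 - GM2/GM1) with GM = 10^(mean of log10(epg+1)) - 1, and state that the same definition applies at 6 and 12 months.
- In section 10.1, remove ERR from the chi-square/Fisher list. Compare the arms on day-21 log10(epg+1), preferably adjusted for baseline log10 epg, and name this as the test for objective 2.2. Report each arm's ERR and their difference with bootstrap confidence intervals.
- Optional, for precision only: replace the change-score t tests for Hb and weight with baseline-adjusted models (ANCOVA). With equal variances at the two times and correlation rho between them, the variance is (1 + rho)/2 of the change-score variance: 25% lower at rho 0.5 and 10% lower at rho 0.8 (both values assumed). The planned tests are valid without this.

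The cost is a few sentences in two sections and a few lines of STATA. No new data, visits or participants are needed.

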#### D0 (means 7 days after baseline study +/-1 day)

Clinical history of each schoolchild fulfilling screening criteria using questionnaire will be taken to see if the subject has acute or chronic severe disease, including hepato-splenic schistosomiasis. In addition, the questionnaire will seek to establish a history of adverse reactions associated with PZQ, a history of treatment with PZQ within 30 days and medication (such as antibiotics) currently being used which may affect the results of the present trial. This will be followed by a thorough physical examination by a physician for physical fitness to participate in the trial. Those showing signs and symptoms of clinical malaria will be referred for treatment and excluded from the study and referred for treatment. Childbearing age female subjects will further be tested for pregnancy using the Quickstick™ One step HCG Pregnancy Test. Those tested positive for pregnancy will be excluded from the study. Each girl will be given individual counseling from the study nurse. Those children with schistosomiasis who will be excluded from the study at this point will be treated with a single oral dose of PZQ at 40mg/kg.

For the children who fulfill all criteria for enrolment, body weight will be determined and a finger-prick blood sample will be collected for Hb measurement. Thereafter they will be treated with PZQ according to weight and dosage regimen assigned in the trial (see randomization and blinding section for treatment assignment). During the 4 hours post-treatment study subjects will be observed for occurrence of adverse events and by the end of this period they will be assessed for adverse events using a questionnaire.

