#### 6.2.2. Stool:

At baseline and during follow-up visits each child in schools within 5 km of the Lake Victoria shore recruited in the study will provide a stool specimen on two separate days at maximum interval of 5 days. Duplicate Kato Katz slides (2 slides) (Katz et al., 1972) will be prepared in the field (using the 41.7mg faecal template) from each stool sample. The prepared Kato slides in the field will undergo quantitative microscopic examination for *S mansoni* ova.

Classification as egg count  $\geq 100$  eggs per gram of faeces for *S mansoni* will be obtained by the mean egg count for the 4 slides collected at baseline.

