### **7. ASSESSMENT OF EFFICACY:**

7.1. Parameter to be measured – egg count, as measured by the Kato-Katz method described above, at baseline, D21, 6M and 12M

The measurement of egg count for each time point will be estimated as the mean of the 4 slides collected (2 slides per sample, 2 samples within 5 days).

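### Section 10.1 fixes unadjusted tests although baseline Hb, weight and egg count are measured in every enrolled child: the tests are valid, but precision is lost, mainly for Hb change and post-treatment egg output

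*Protocol*

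**What the plan says.** Section 10.1 is the only place where the protocol names tests. For cure and the other outcomes that it treats as proportions: "Chi- square or Fisher's exact test will be used for comparison of proportions". For the continuous outcomes it names Student's t test "for comparison of means (geometric mean egg output, variation of Hb level and weight". Sections 7.3, 8.3 and 9.3 say only that the two regimens will be compared. No regression, stratified or covariate-adjusted analysis appears anywhere in the protocol.

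Two secondary endpoints in section 3.2 are defined as changes from baseline: "Comparison of the variation of hemoglobin (Hb) level at 21 days, 6 months and 12 months after treatment (as related to the baseline measurement") and "Comparison of the variation of weight at 6 months and 12 months after treatment (as related to the baseline measurement").

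The baseline values exist for every enrolled child. At the D0 visit, before treatment, "body weight will be determined and a finger-prick blood sample will be collected for Hb measurement". For eggs, section 6.2.2 says that classification against the entry threshold "will be obtained by the mean egg count for the 4 slides collected at baseline", and section 7.1 lists egg count as measured "at baseline, D21, 6M and 12M".

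Randomisation (section 3.3) is 1:1 in blocks of 4, with no stratification by infection intensity.

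**The concern.** In a randomised comparison, a baseline measurement that predicts the outcome can be put in the model at no cost in data, and it removes outcome variation that has nothing to do with treatment. Section 10.1 does not do this.

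- **Hb and weight.** The t test on change scores subtracts the whole baseline value, which fixes the slope on baseline at 1. ANCOVA estimates the slope. If the true slope is below 1, subtracting everything adds noise. Section 5.2 gives iron to anaemic children, which may weaken the link between baseline and later Hb.
- **Egg output.** If the t test compares post-treatment values only, the baseline count is not used at all.
- **Cure.** The protocol itself ties intensity to measured cure: section 12.1 worries about missed eggs in light infections, and the introduction reports low cure rates from a very intense focus. The chi-square test does not use intensity.

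At stake are wider intervals than necessary for the Hb and egg endpoints, and possibly some precision on the primary endpoint.

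**Working it through.** **1. The plan's own figure.** Inputs from section 10.2: cure 60% v 80%, 5% significance, 80% power. Two-sided, without continuity correction:

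n = [1.960 x sqrt(2 x 0.7 x 0.3) + 0.842 x sqrt(0.6 x 0.4 + 0.8 x 0.2)]^2 / 0.2^2 = 81.2, so 82 per arm.

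With continuity correction: (81.2/4) x [1 + sqrt(1 + 4/(81.2 x 0.2))]^2 = 90.95, so 91. This matches the protocol exactly. The trial was sized for an unadjusted test of cure.

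**2. Hb and weight: ANCOVA against the change-score t test.** Let rho be the correlation between baseline and follow-up, and k the ratio of the follow-up SD to the baseline SD. The variance ratio is

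k^2 (1 - rho^2) / (1 + k^2 - 2 rho k), which is (1 + rho)/2 when k = 1.

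The protocol gives neither rho nor k, so rho is an assumed range. The last column is ANCOVA power where the t test has 80%: Phi(2.802/sqrt(ratio) - 1.960).

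| rho (k = 1) | Variance ratio | Reduction | ANCOVA power |
|---|---|---|---|
| 0.4 | 0.70 | 30% | 91.8% |
| 0.5 | 0.75 | 25% | 89.9% |
| 0.7 | 0.85 | 15% | 86.0% |
| 0.9 | 0.95 | 5% | 82.0% |
| 0.95 | 0.975 | 2.5% | 81.0% |

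At rho = 0.5 the gain is worth 1/0.75 = 1.33 times as many children.

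Equal variances matter here. With rho = 0.95 and k = 1.05 the slope is rho x k = 0.9975, and the ratio is 1.1025 x 0.0975 / (1 + 1.1025 - 1.995) = 0.9999. With rho = 0.90 and k = 1.10 it is 0.9996. Where the true slope is 1, the change score loses nothing.

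**3. Egg output: ANCOVA against a t test on post-treatment values only.** The ratio is 1 - rho^2.

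| rho | Variance ratio | Reduction | ANCOVA power where the t test has 80% |
|---|---|---|---|
| 0.3 | 0.91 | 9% | 83.6% |
| 0.4 | 0.84 | 16% | 86.4% |
| 0.5 | 0.75 | 25% | 89.9% |

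**4. Cure.** Two simulations used 91 per arm and true marginal cure rates of 60% and 80%. The unadjusted test is the chi-square without continuity correction. The odds ratio is per SD of baseline log egg count and is assumed.

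| Odds ratio per SD | Trials | Chi-square power | Adjusted logistic power | Variance of standardised risk difference v unadjusted |
|---|---|---|---|---|
| 1 | 4,000 | 0.842 | 0.840 | 1.00 |
| 1.5 | 4,000 | 0.848 | 0.852 | 0.98 |
| 1.65 (log-odds 0.5) | 1,500 | 0.848 | 0.858 | not computed |
| 2 | 4,000 | 0.852 | 0.875 | 0.93 |
| 2.5 | 4,000 | 0.842 | 0.887 | 0.87 |
| 2.72 (log-odds 1.0) | 1,500 | 0.838 | 0.896 | not computed |
| 3 | 4,000 | 0.844 | 0.903 | 0.85 |

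The gain is nil with no prognostic value, about 1 point at an odds ratio of about 1.6, and about 5-6 points at about 2.7. Each power estimate has a Monte Carlo standard error of about 0.009 (1,500 trials) or 0.006 (4,000 trials), so differences of 1 point are not sharply determined.

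**The case against.** The strongest reply is that nothing here is an error. Chi-square, Fisher and t tests are valid in a 1:1 randomised trial, and the primary test is the one that the sample size was built on. That stands: the point concerns efficiency only. It is also why the chi-square test should not be displaced for cure.

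A second reply is that adjustment belongs in a statistical analysis plan, which is not at hand and may add it. That carries less weight, because the protocol does not leave the tests open. It names them.

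Several stronger readings are tempting, and the document does not support them:

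- **A reader might infer that baseline is ignored.** It is not. The Hb and weight endpoints subtract it, and the egg reduction rate in section 7.2 divides by it. For Hb and weight the remaining complaint is only that the slope is fixed rather than estimated.
- **A reader might infer that chance imbalance in baseline intensity passes straight into every egg result.** That does not describe the egg reduction rate. It could apply to the t test on egg output, but section 10.1 gives no time point for that test, so treating it as post-treatment only is an interpretation.
- **A reader might infer that ANCOVA beats the change score at every correlation below 1.** That needs equal variances. In children aged 10-19 followed for 12 months the SD of weight could rise, and the advantage could then vanish.
- **A reader might infer a firm loss of power on the primary endpoint.** No passage gives the prognostic strength of baseline egg count, and the entry rule of at least 100 eggs per gram narrows its range from below.

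**Conclusion.** The point holds as avoidable loss of precision, not as bias or invalidity. Section 10.1 fixes unadjusted tests while the relevant baselines are already collected.

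The loss is most likely to matter for Hb change and for post-treatment egg output, if the latter is compared without baseline. At the planned cure rates most D21 counts would be zero, which may keep the egg correlation towards the lower end of the assumed range. For weight the gain is close to nil at the high correlation that is plausible there. For cure it is uncertain and may be nil.

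The direction is secure, since estimating the slope costs essentially nothing at this sample size. The magnitudes are conditional on correlations, equal variances and prognostic strength that the protocol does not state.

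**What to change.** In section 10.1, before any outcome data are seen:

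- Analyse Hb (D21, 6 and 12 months) and weight (6 and 12 months) at each visit by a linear model on arm plus the baseline value of the same measure. The arm coefficient is the baseline-adjusted difference in change.
- Analyse log10(epg+1) at D21 by a linear model on arm plus baseline log10(epg+1). Back-transform the arm coefficient to a ratio of geometric means (of epg+1) with a 95% confidence interval.
- Keep the chi-square test for cure, which matches the sample size. Add a prespecified standardised risk difference with a 95% confidence interval, from a logistic model on arm and baseline log10 epg. The risk-difference scale is preferable because an adjusted odds ratio is a conditional effect whose standard error need not fall. With the chi-square test kept, its power is unchanged and any gain appears in this interval.

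The cost is one paragraph of analysis wording. No new data, visits or children are needed, and the 91 per arm is unaffected.
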